#### Main research question

The primary and secondary endpoints will be analyzed according to the intention-to-treat principle. Treatment effects (between-group effects) in primary and secondary outcomes will be evaluated using analysis of covariance (ANCOVA) adjusting for baseline values. Statistical significance (*p* < 0.05, two-sided) and effect sizes (*ή*^2^) will be reported for all between-group differences [27]. In addition, within-group effects, including standardized effect sizes (SES) and accompanying 95% confidence intervals (CIs), will be calculated for both study groups.

#### Secondary research question

We will also use ANCOVA adjusting for baseline values to examine the group differences in patients’ mental well-being by psycho-oncological support of their relatives (less than two consultations versus at least two consultations).

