## Objectives

Our study aims to prove the effectiveness of a structured psycho-oncological intervention based on the CALM (CALM intervention) compared to usual care for relatives of lung cancer patients. In a randomized controlled study, we examine the following research questions:

The following are the main research questions:Does a CALM intervention for relatives of lung cancer patients (IG) reduce the extent of self-reported anxiety *(primary outcome*) compared to usual care (CG)?Does a CALM intervention for relatives of lung cancer patients (IG) reduce self-reported symptoms of depression, distress, and supportive care needs while increasing quality of life (*secondary outcomes*) compared to the CG?

We hypothesize that the CALM intervention for relatives of lung cancer patients reduces the extent of reported anxiety among relatives (*primary hypothesis*). In addition, we expect superior effectiveness of the CALM intervention regarding depression, distress, supportive care needs, and quality of life.

As a *secondary research question*, we explore the impact of psycho-oncological support of relatives on the patients’ mental health outcomes.Does the psycho-oncological support of relatives positively affect patients’ levels of depression, anxiety, and distress indirectly?

We expect that a supported and resource-empowered relative has an indirect positive effect on the patient’s well-being.

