### Intervention

#### Intervention group (IG)

The intervention condition is a structured psycho-oncological intervention based on the Managing Cancer And Living Meaningfully (CALM) manual. CALM is an individualized, evidence-based psychotherapeutic intervention that focuses on four domains relevant to the challenges typically experienced by cancer patients:Symptom management and communication with healthcare providersChanges in self and relations with close othersSpiritual well-being and a sense of purposeConcerns related to the future and mortality [28]

The topics covered in the CALM domains are also relevant for relatives. Adaptations of the intervention therefore refer to the fact that in all domains, the well-being (e.g., physical and psychological symptoms) and the self-perception of the relative (e.g., change in values since the relative’s illness) are explored instead of the well-being and perception of the patient.

The CALM domains should be addressed in a tailored, individualized manner that allows for variation in time spent on each domain and the number of sessions based on the participants’ needs. Therefore, each relative receives three to six counseling sessions, each lasting 45 min. A CALM-trained psychologist delivers the sessions within 6 weeks. Three psychologists of the CCCMF (experienced psycho-oncologists/psychotherapists) were trained to do the CALM intervention at the psycho-oncological department.

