#### Control group (CG)

Relatives of the CG receive written information about the offers (e.g., counseling, relaxation groups) of psycho-oncological care at the CCCMF by giving the patient the information flyer of the psycho-oncological department. This offer of psycho-oncological care with single and group interventions for patients and relatives corresponds to usual care. Therefore, psycho-oncological counseling is also possible in the CG but is based on personal needs and active engagement. This needs-based counseling in usual care is not structured according to the CALM approach. Furthermore, it is not standard to schedule as many counseling sessions within 6 weeks. This control condition was chosen for ethical reasons.

No specific psycho-oncological intervention is proactively offered to the lung cancer patients in both study arms. However, they can request the support of the psycho-oncological team of the CCCMF (usual care).

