### Assignment of interventions

#### Randomization and allocation concealment

All participants, i.e., dyads of relatives and lung cancer patients, will be randomly assigned to IG or CG after consent is given and initial questionnaires (T0) are completed.

A block randomization procedure with an allocation ratio of 1:1 is used. A member of the study center (not involved in the study) created the randomization list with computer-generated random numbers linked to the research codes (i.e., a consecutive list of numbers). The research code is used on all questionnaires and medical data instead of the name (pseudonymization; see confidentiality). The list is stored locked at the study center. Research codes are printed on the first questionnaires (T0). Therefore, assignment based on the sequence of the list is determined by the time of receipt of the interest to participate and, consequently, the distribution of the study information, consent form, and questionnaire. Allocation concealment will be ensured, as the study members responsible for enrollment (i.e., study coordinator) will not release the randomization number until the signed consent form and baseline assessments have been completed.

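### The only analysis named for the patient question groups patients by how many consultations the relative took, not by randomised arm, so it cannot show the effect of supporting the relative

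*Protocol article*

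**What the plan says.** The Objectives section poses the patient question in causal terms: "Does the psycho-oncological support of relatives positively affect patients’ levels of depression, anxiety, and distress indirectly". It describes the question as exploratory but states the expected direction, an indirect benefit to the patient.

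The Secondary research question section, under Statistical analysis, gives the analysis: "We will also use ANCOVA adjusting for baseline values to examine the group differences in patients’ mental well-being", with groups defined by "psycho-oncological support of their relatives (less than two consultations versus at least two consultations". The baseline value is the only covariate named.

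The randomised structure is set out under Randomization and allocation concealment: "All participants, i.e., dyads of relatives and lung cancer patients, will be randomly assigned to IG or CG", and "A block randomization procedure with an allocation ratio of 1:1 is used". Each patient is therefore allocated together with the relative. Tables 1 and 2 have patients in both arms completing GAD-7, PHQ-9 and DT at T0 and T1.

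Two statements bear on who reaches two consultations. For the control group, "psycho-oncological counseling is also possible in the CG but is based on personal needs and active engagement". For the intervention group, "each relative receives three to six counseling sessions, each lasting 45 min", but the Discussion adds that relatives may decline sessions at any time.

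**The concern.** Randomising the dyad makes the patients in the two arms comparable. Regrouping them by the relative's consultation count gives that up for this comparison. Control relatives who sought two or more usual-care contacts are placed with CALM recipients, and intervention relatives with none or one are placed with controls.

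Who crosses the line is not random. In the control arm the protocol says counselling follows need and active engagement; in the intervention arm it depends on willingness to continue. Both can follow the patient's course over the six weeks. A worsening patient may lead a relative to seek more sessions or leave the relative unable to attend, so the direction of bias is not known in advance. The T0 score cannot adjust for events after T0.

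At stake is the reading of the patient result. A difference between the groups could be reported as a benefit or harm of supporting the relative when it only reflects which relatives attended.

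**Working it through.** **1. The plan's own figure, used as an input.** For d = 0.4, two-sided alpha 0.05 and power 0.80, the normal formula gives n per arm = 2(1.960 + 0.842)² / 0.4² = 98.1, so 99 per arm. The t-based calculation gives 99.08, so 100 per arm and 200 in total. The stated 200 is reproduced. It was set for the relatives' GAD-7; here it only supplies 100 dyads per arm.

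**2. Assumptions.** The documents give no uptake rates, no T0–T1 correlation and no association between attendance and the patient's course. Assumed here:
- no true effect on patients;
- T0–T1 correlation 0.5, so the T1 residual SD after T0 adjustment is √(1 − 0.5²) = 0.866 of the outcome SD;
- a relative reaches two consultations when a latent normal variable passes an arm-specific threshold, with uptake p₁ (IG) and p₀ (CG);
- that variable has correlation ρ with the patient's post-baseline residual.

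**3. Formulas.** Let P = (p₁ + p₀)/2 and M = [φ(z₁) + φ(z₀)]/2, where φ is the normal density at the quantile of each uptake rate. Then:
- spurious difference in SD = ρ × 0.866 × M / [P(1 − P)]
- expected z = ρ × M × √(200 / [P(1 − P)])
- rejection rate ≈ Φ(z − 1.96) + Φ(−z − 1.96)

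Reversing the sign of ρ reverses the bias and leaves the rejection rate unchanged.

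**4. Example.** Take p₁ = 0.85, p₀ = 0.25, ρ = 0.3. M = (0.2332 + 0.3178)/2 = 0.2755; P = 0.55; P(1 − P) = 0.2475. Spurious difference = 0.3 × 0.866 × 0.2755/0.2475 = 0.29 SD. z = 0.3 × 0.2755 × √(200/0.2475) = 2.35. Rejection ≈ Φ(0.39) = 0.65; simulation gives 0.66.

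**5. Results for ρ = 0.1 / 0.2 / 0.3.**

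| Uptake IG / CG | M | P(1 − P) | Spurious difference (SD) | Rejection, formula | Rejection, simulation |
|---|---|---|---|---|---|
| 95% / 5% | 0.1031 | 0.2500 | 0.04 / 0.07 / 0.11 | 6 / 9 / 14% | 6 / 9 / 13% |
| 85% / 10% | 0.2043 | 0.2494 | 0.07 / 0.14 / 0.21 | 9 / 21 / 41% | 9 / 21 / 41% |
| 85% / 25% | 0.2755 | 0.2475 | 0.10 / 0.19 / 0.29 | 12 / 35 / 65% | 12 / 34 / 66% |

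Under the same model the ANCOVA by randomised arm rejects in about 5% of trials in every row, with bias about zero. At ρ = 0 the consultation split also holds about 5%. The excess therefore comes from self-selection, not from splitting as such.

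**6. Does another section already supply the arm comparison?**
- Outcomes and measurements lists depression and distress as secondary outcomes for patients as well as relatives.
- The sentence closing the Quality of life subsection says primary and secondary outcomes are compared between IG and CG at T1.
- The statistical section applies intention to treat and baseline-adjusted ANCOVA to primary and secondary endpoints, but under the heading Main research question, which Objectives limits to relatives.
- Patients' anxiety is not named among the secondary outcomes. Anxiety is listed as the primary outcome, which Objectives and the Abstract define for relatives.

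An arm comparison of patients' depression and distress can be inferred from these sections. One for patients' anxiety is not clearly there, and the section written for the patient question mentions neither.

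**The case against.** A reader might infer that the plan abandons the randomisation for patients altogether. The documents do not support that. The three statements in step 6 can be read together as an intention-to-treat comparison by arm for at least two patient outcomes, and the patient analysis is introduced with the word also, which may mean an addition. This part of the objection stands: the arm comparison for patients is unclear, not shown to be excluded.

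The question is also exploratory. The primary outcome, sample size and interim rule concern relatives, and none depends on this analysis. That limits the severity, but it is no reason to answer a causal question with a self-selected grouping when the randomised one is at hand.

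The size rests on assumptions. Intervention relatives are meant to have at least three sessions and control relatives are not actively contacted, so crossover may be low; the 95% / 5% row then applies and the inflation is modest. The 66% figure is not an expected result.

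Two further readings are tempting and do not hold as separate errors. The cut-off of two does not contradict the planned minimum of three sessions, since one describes exposure received and the other the intended dose. The Discussion's comparison of relatives with few and more conversations is offered as an additional interest, not as a replacement for the intention-to-treat analysis.

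**Conclusion.** The point holds in this form: the only analysis named for the patient question is a non-randomised split, adjusted for T0 alone, and its result cannot be read as the effect of supporting the relative on the patient. Whether patients are also compared by arm is left ambiguous for depression and distress, and is not clearly provided for anxiety.

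Under the stated assumptions the false-positive rate ranges from barely above nominal, when crossover is low and attendance is weakly related to the patient's course, to about two thirds in the least favourable setting examined. That the split is exposed to this bias and the arm comparison is not does not depend on the chosen values; the size does. The point should be fixed, but it does not threaten the trial's primary conclusion.

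**What to change.** In the Secondary research question section, make the main analysis of patients' GAD-7, PHQ-9 and DT an intention-to-treat ANCOVA by randomised arm (IG versus CG), adjusted for the patient's own T0 value. State there that all three outcomes are covered, so that nothing has to be inferred from the section on the main research question. Keep the comparison of fewer than two with at least two consultations as a supplementary analysis, labelled non-randomised.

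If the effect of sessions actually received is of interest, randomised arm could serve as an instrument for the session count. That is optional and assumes that allocation affects the patient only through the relative's sessions.

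The cost is wording only, since allocation and patient questionnaires are already part of the planned data. The arm contrast is diluted by counselling taken up in the control group, but that uptake does not bias it as an estimate of the effect of allocation. Because the analysts are not blinded, the change should be made before any patient comparison is run.

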#### Interim analysis

Due to heterogeneous results and high effort in recruiting this vulnerable group, we plan an interim analysis on the primary endpoint with *n* = 88 persons (sample size showing a medium effect size *d* = 0.6). The study team will discuss the results and decide on the continuation of the trial. Pre-specified criteria are as follows: The trial will be closed when there is a medium effect of *d* = 0.6 or smaller effects than *d* = 0.4. Recruitment will be continued until the calculated sample size if the effect is about *d* = 0.4.

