### Sample size calculation

A recent systematic review of interventions for relatives of cancer patients with partly different tumor entities showed heterogeneous results. Many of the included studies showed nonsignificant improvements in outcomes due to insufficient power [25]. Following previous intervention studies with this patient group, which focus on the support of relatives, an effect size of *d* = 0.4 is set [25]. To demonstrate an effect of *d* = 0.4 in the primary outcome (GAD-7) at a significance level of alpha = 0.05 and beta = 0.2 for comparing two independent samples, *n* = 200 relatives are required (100 per group). Due to heterogeneous results and high effort in recruiting this vulnerable group, we plan an interim analysis with *n* = 88 persons (44 per group; sample size showing a medium effect size *d* = 0.6). The trial will be closed if the effect size is *d* = 0.6 or *d* < 0.4. A member of the statistical consulting of the Institute of Clinical Epidemiology, University of Würzburg, supported sample size calculation.

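### The lower interim stopping limit equals the design effect of d = 0.4, so the stated beta = 0.2 does not hold: power is about 48% on a strict reading and still below 80% on lenient ones

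*Protocol article*

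**What the plan says.** Protocol article, Sample size calculation: the trial is sized "To demonstrate an effect of *d* = 0.4 in the primary outcome (GAD-7) at a significance level of alpha = 0.05 and beta = 0.2", which gives 200 relatives, 100 per group. The same section plans an interim analysis of 88 persons, 44 per group, and states: "The trial will be closed if the effect size is *d* = 0.6 or *d* < 0.4".

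Protocol article, Interim analysis: the rule is repeated as a pre-specified criterion, "The trial will be closed when there is a medium effect of *d* = 0.6 or smaller effects than *d* = 0.4". Two further statements in this section bear on how strictly it applies. The study team discusses the interim results and decides whether to go on, and recruitment runs to the full sample size if the effect is approximately 0.4. No width is given for that approximation.

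Protocol article, Main research question: the primary test is an ANCOVA adjusted for baseline, two-sided at 0.05. The sample size, in contrast, is for a plain comparison of two independent samples. Neither section adjusts the power statement for the interim rule.

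**The concern.** A futility limit is normally set well below the effect that the trial is designed to detect, because an interim estimate from fewer than half the participants is imprecise. Here the limit sits at the design effect. When CALM works exactly as hypothesised, the interim estimate is centred on the limit, and about half of all such trials fall on the wrong side of it. The 80% power belongs to a fixed design of 200 with no look, not to the design described.

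This matters because the article itself attributes many nonsignificant results in earlier studies to insufficient power, and its Discussion asks for well-powered trials. A closure caused by this rule could be read as evidence that CALM does not help relatives when it says little either way.

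**Working it through.** **Inputs.** From Sample size calculation: d = 0.4, alpha 0.05, beta 0.2, 100 per group, interim at 44 per group. From Main research question: two-sided testing. From Randomization and allocation concealment: 1:1 allocation.

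**Step 1: reproduce the plan's figures.** n per group = 2(1.96 + 0.8416)² / d².
- d = 0.4: 15.70 / 0.16 = 98.1, so 99 per group (100 stated).
- d = 0.6: 15.70 / 0.36 = 43.6, so 44 per group (44 stated).
- Power at 100 per group for d = 0.4: Φ(0.4/√(2/100) − 1.96) = Φ(0.87) = 80.7%, or 80.4% by the t distribution.

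The fixed-design calculation is sound.

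**Step 2: the interim look when the true d is 0.4.** The standard error of the interim estimate is √(2/44) = 0.213.
- P(estimate < 0.4) = Φ(0) = 50%.
- P(estimate ≥ 0.6) = 1 − Φ(0.2/0.213) = 17% (18% in a t-test simulation).
- The remaining 32–33% continue to 200.

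**Step 3: overall power under the strict rule.** A low closure counts as no success, a closure at d ≥ 0.6 is tested at n = 88, and all others are tested at n = 200, each at two-sided 0.05. Simulation gives 47.8% (normal approximation, 400,000 replicates) and 48.1% (t tests on raw data, 200,000 replicates). Low closures alone cap power at about 50%. In the unadjusted comparison they cannot be rescued by testing at n = 88, because significance there needs an estimate of about 1.96 × 0.213 = 0.42.

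For larger true effects the strict rule gives 67% power at d = 0.5 (94% without the look) and 82% at d = 0.6 (99% without the look).

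**Step 4: vary the lower limit L.** P(closed low) is Φ((L − 0.4)/0.213) when the true d is 0.4 and Φ(L/0.213) when there is no effect. Power is from simulation.

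| Lower limit L | Closed low, true d = 0.4 | Power, true d = 0.4 | Closed low, no effect |
|---|---|---|---|
| 0.40 | 50% | 48% | 97% |
| 0.35 | 41% | 56% | 95% |
| 0.30 | 32% | 63% | 92% |
| 0.25 | 24% | 69% | 88% |
| 0.20 | 17% | 73% | 83% |
| 0.10 | 8% | 78% | 68% |
| 0 | 3% | 80% | 50% |

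**Step 5: what a low closure gives up.** At n = 200, significance needs an estimate of only 1.96 × √(2/100) = 0.28. Given interim estimate d₁, the second-stage estimate must reach (100 × 0.277 − 44 × d₁)/56, with standard error √(2/56) = 0.189. Conditional power under d = 0.4:
- d₁ = 0.30: required 0.259; Φ((0.4 − 0.259)/0.189) = 77%.
- d₁ = 0.20: required 0.338; Φ((0.4 − 0.338)/0.189) = 63%.

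**Step 6: baseline adjustment.** The documents give no T0–T1 correlation, so 0.3 to 0.7 is an assumption. If low closures count as failures, power stays at 48–50%, because the adjusted estimate is still centred on the limit. If low-closed trials were tested by ANCOVA at n = 88 and a significant result counted, the estimate needed would be 0.418 × √(1 − ρ²): 0.36 at ρ = 0.5 and 0.30 at ρ = 0.7. Power would then be about 58% and 75%. Without the look, the same ANCOVA at 100 per group would have Φ(0.4/(0.1414 × 0.866) − 1.96) = 90% and Φ(0.4/(0.1414 × 0.714) − 1.96) = 98%.

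**The case against.** A reader might infer that the trial must close whenever the interim estimate is below 0.4, so that 48% is simply its power and failure is more likely than success. The documents do not go that far. The Interim analysis section also says to continue when the effect is roughly 0.4, and an estimate of 0.39 is the case this most naturally covers. It gives the decision to the study team as well. With a limit of 0.35, power is about 56%, so failure is no longer the likelier outcome. Nor can one say that baseline adjustment is no help at all: if closed trials are still analysed by ANCOVA, some low closures reach significance.

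The counterweight is that both sections say the trial will be closed, the criteria are called pre-specified, and Sample size calculation gives the limit without softening. The tolerance has no stated width. More important, every lower limit from 0.20 to 0.40 leaves power between 48% and 73%, and both ANCOVA figures (58% and 75%) are below 80% too.

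It can also be said that stopping early for small effects is a deliberate resource choice, since the article cites recruitment effort and staff resources. That is a legitimate aim and explains why there is a look. The article does not call 0.4 a minimum worthwhile effect, however, and the resource argument does not make the beta = 0.2 statement true.

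**Conclusion.** The point stands. The lower interim limit is the design effect, and the stated power is not a property of the design described. At a true d of 0.4, power is about 48% under the strict limit, against 80% with no interim. It is about 56% to 73% if the undefined tolerance is read as a limit of 0.35 down to 0.20. The 48% is the strict reading, not the only one, and should be quoted as such.

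The figures assume normal data with equal variances, no dropout (the documents give no rate), an upper closure at d ≥ 0.6 tested at n = 88, and no success claimed after a low closure. Relaxing the last assumption under ANCOVA gives about 58% at an assumed correlation of 0.5 and 75% at 0.7.

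**What to change.** Before any interim result is seen, replace the d < 0.4 criterion and the undefined tolerance around 0.4 by one explicit, non-binding futility limit well below the design effect. Use the same wording in Sample size calculation and Interim analysis. Two examples:
- Close low only if the interim d is at or below 0: 3% closed under d = 0.4, power about 80%, 50% closed under no effect.
- Close low only if the interim d is below 0.10: power about 78%, 68% closed under no effect.

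The choice between such limits is the sponsor's trade-off of power against resources. If the present limit is kept, the power in Sample size calculation should be restated as about 48% for d = 0.4.

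**Cost.** A protocol amendment is needed. Under Ethics, consent, and permission, changes go to the ethics committee for approval; the interim analysis itself was submitted on 22.11.2022 and approved on 19.12.2022. The maximum of 200 is unchanged. The expected sample size, 88 + 112 × P(continue), rises. At true d = 0.4 it goes from 88 + 112 × 0.326 ≈ 125 under the strict limit to 88 + 112 × 0.796 ≈ 177 with a limit of 0. Under no effect it goes from 88 + 112 × 0.028 ≈ 91 to 88 + 112 × 0.498 ≈ 144.

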#### Blinding

Blinding of participants and psycho-oncologists is not possible due to the active counseling intervention. However, psycho-oncologists are not involved in recruitment and data collection. Other care providers are blind to study participation and/or assignment. For organizational reasons, the analysts will not be blinded. The members of the study team will each take on several tasks. They are responsible for enrollment, data collection, management, and statistical analysis.

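### The interim rule rests on the observed d alone, overlaps just below 0.4, gives no explicit action between about 0.4 and 0.6 and assigns no alpha, so its error rates depend on how an unblinded study team reads it

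*Protocol article*

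**What the plan says.** The Sample size calculation section of the protocol article plans on the primary outcome, the GAD-7: "an effect size of *d* = 0.4 is set", tested "at a significance level of alpha = 0.05 and beta = 0.2", so that "200 relatives are required (100 per group"). It adds an interim analysis at 88 persons, 44 per group, and gives the closing conditions: "The trial will be closed if the effect size is *d* = 0.6 or *d* < 0.4".

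The Interim analysis section repeats these two conditions as pre-specified criteria and adds a condition for going on: "Recruitment will be continued until the calculated sample size if the effect is about *d* = 0.4". On who decides, it says: "The study team will discuss the results and decide on the continuation of the trial".

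The Main research question section specifies ANCOVA adjusting for baseline, with significance at p < 0.05, two-sided. Neither that section nor the two that describe the interim look gives an interim significance level or an adjusted final level.

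The Blinding section states: "For organizational reasons, the analysts will not be blinded". It also says that the team members carry out enrolment, data collection, data management and statistical analysis.

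**The concern.** A stopping rule has defined error rates only if every possible interim result leads to exactly one action and the final test allows for the earlier look. This rule does neither.

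- **Overlap.** An observed 0.38 is smaller than 0.4, so the trial closes. It is also about 0.4, so the trial continues.
- **Gap.** An observed 0.50 is neither 0.6 nor plainly about 0.4.
- **No alpha.** The full 0.05 is used for the final test, although closing at 0.6 ends the trial on the primary endpoint.
- **Discretion.** The people who enrol and follow up participants see the estimate and settle the unclear cases in discussion. The outcome is self-reported, and the same team goes on collecting data if the trial continues.

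At stake are the meaning of the reported p-value, the size of the reported effect if the trial closes early, and the power that the sample size was meant to secure.

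**Working it through.** **Inputs from the protocol article.** Design d = 0.4; two-sided alpha 0.05; power 80%; 100 per group at the end; 44 per group at the interim; limits at d = 0.6 and d = 0.4.

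**The plan's own sizes.** n per group = 2(1.960 + 0.842)²/d². For d = 0.4 this is 15.70/0.16 = 98.1, so 99. For d = 0.6 it is 15.70/0.36 = 43.6, so 44. Power is 80.7% at 100 per group and 80.4% at 44 per group. Both stated sizes are reproduced.

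**Interim scale.** Unadjusted, z = d·√(44/2) = 4.690·d.
- d = 0.6: z = 2.81, two-sided p about 0.005.
- d = 0.4: z = 1.88, two-sided p about 0.06.

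**Joint distribution.** The interim and final statistics are bivariate normal with correlation √(88/200) = √0.44 = 0.663. The final critical value is 1.96.

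**Type I error by reading** (unadjusted comparison):

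| Reading | One-sided (nominal 2.5%) | Two-sided (nominal 5%) |
|---|---|---|
| Close at d ≥ 0.6 as success, stop below 0.4, continue in between, all binding | 0.95% | – |
| As above, but success from d ≥ 0.5 | 1.4% | – |
| Stop only at 0.6, otherwise continue to 200 | 2.6% | 5.2% |
| Success at d ≥ 0.5, otherwise continue to 200 | 3.1% | – |
| Outside the stated criteria: p < 0.05 at either look | 4.3% | 8.5% |

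**How often the unclear zone is reached.** If true d = 0.4, the interim estimate has standard error √(2/44) = 0.213. P(0.4 ≤ d̂ < 0.6) = Φ(0.2/0.213) − 0.5 = 0.826 − 0.5 = 33%.

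**Early closure at 0.6 when true d = 0.4.** P(d̂ ≥ 0.6) = 1 − Φ(0.938) = 17.4%. Mean reported d in those trials = 0.4 + 0.213 × φ(0.938)/0.174 = 0.4 + 0.213 × 1.476 = 0.71.

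**Power when true d = 0.4.** A binding stop below 0.4 ends half of such trials, because the estimate is centred on 0.4. Adding the 17.4% that close at 0.6 to the continuing trials that reach significance gives 47.8%. If the stop is not binding, power is 80.9%.

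**Sensitivity to ANCOVA.** Take d as the adjusted difference over the raw SD. The standard error then shrinks by √(1 − ρ²), where ρ is the baseline–T1 correlation. The article gives no ρ, so these values are assumptions:

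| ρ | z at d = 0.6 | Two-sided error, stop only at 0.6 | P(close at ≥ 0.6), true d = 0.4 | Mean d if so closed | d at which z = 3.0 |
|---|---|---|---|---|---|
| 0 | 2.81 | 5.2% | 17% | 0.71 | 0.64 |
| 0.3 | 2.95 | 5.1% | 16% | 0.71 | 0.61 |
| 0.5 | 3.25 | 5.0% | 14% | 0.69 | 0.55 |
| 0.6 | 3.52 | 5.0% | 12% | 0.68 | 0.51 |

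The loss from a binding lower limit does not go away with ρ. It still ends half of the trials with true d = 0.4, so power cannot exceed 50%.

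**Check of a repaired rule.** With interim |z| ≥ 3.0 (two-sided p = 0.0027), an overall two-sided 0.05 needs a final z of 1.969, p = 0.0489. Power at d = 0.4, unadjusted, is 80.6% against 80.7% with a single look.

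**The case against.** The strongest reply is that the written criteria barely inflate alpha. If both limits are followed, the error is below nominal. If only 0.6 stops the trial, the excess is about 0.2 points, and less with ANCOVA. This stands. A reader might infer from the missing alpha allocation that the trial runs at 8.5%. The documents do not support that, because the stated criteria are effect sizes and 8.5% requires closing on an interim p < 0.05.

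Second, the Sample size calculation section lists only closing conditions, so continuing from 0.4 up to 0.6 follows by exclusion. That would be a fair reading of that section alone. The Interim analysis section, however, ties continuation to an effect of about 0.4, which blurs the upper range and creates the overlap below 0.4.

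Third, one could say that values above 0.6 are not covered. That is too literal: a team that closes at 0.6 would close at 0.7. Nor is it an error that an observed d ≥ 0.6 occurs only half the time when the true d is 0.6, since the article claims no power for the stopping rule.

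Fourth, boundaries and adjusted levels are often left to an analysis plan, and the article openly gives organizational reasons for unblinded analysts. But the article prints the rule as pre-specified, in two sections with different wording, beside an unadjusted p < 0.05. The fault lies in what is printed.

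**Conclusion.** The concern holds as a defective stopping rule. It does not hold as proven alpha inflation. The printed rule overlaps just below 0.4, gives no explicit action between about 0.4 and 0.6, allots no alpha to the look, and leaves unclear cases to an unblinded team that also recruits and collects data.

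Under the stated criteria, type I error runs from about 1.0% one-sided with both limits binding to about 5.2% two-sided with only the 0.6 limit in force. The larger effects lie elsewhere. Power at the design effect falls to about 48% if the lower limit binds. If true d = 0.4, about 17% of trials close at 0.6 or above and report a mean d of about 0.71.

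These figures assume normal statistics, an information fraction of 0.44 and, unless stated, an unadjusted comparison. They also take closure at 0.6 as a claim of success, which is the natural reading but is not said outright. The documents show no bias from the team's access to interim results; they show only that nothing guards against it.

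**What to change.** Replace the wording in the Sample size calculation and Interim analysis sections with one exhaustive, non-overlapping rule on the ANCOVA test statistic:

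- **Efficacy.** For example, close only if interim |z| ≥ 3.0. In every other case continue to 200 and test the final analysis at two-sided p < 0.0489.
- **Lower limit.** Declare the limit at d < 0.4 explicitly non-binding, or keep it binding and restate the power with it in force (about 48% at d = 0.4, unadjusted).
- **Scale.** Do not translate the z boundary into d without stating the assumed baseline–T1 correlation. z = 3.0 is d = 0.64 at zero correlation but about 0.55 at 0.5.
- **Estimate.** If the trial closes early, report an effect estimate adjusted for early stopping.
- **Access.** Where feasible, let the statistical consulting unit that supported the sample size run the look and pass on only 'close' or 'continue'.

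The cost is wording and one extra task for the consulting unit. The sample size does not change, and with the lower limit non-binding the adjusted final level costs about 0.2 points of power.
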